##### Pattern Identification for Chronic Cough Questionnaire

The Pattern Identification for Chronic Cough Questionnaire (PICCQ) is used to identify patterns in chronic cough patients. We developed this questionnaire using the Delphi method [32], and conducted clinical research to confirm its validity and reliability. The PICCQ consists of four patterns: wind-cold, phlegm-turbidity, fire-heat, and deficiency (lung deficiency and kidney yang deficiency). The PICCQ comprises 38 items scored on 5-point Likert scales. A patient’s pattern is calculated by summing the scores of each item. We will investigate the chronic cough pattern distribution in chronic dry cough patients, as well as the correlation between chronic cough pattern and the efficacy of MMDT.

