##### Cold-Heat Pattern Questionnaire

We will use the validated Cold-Heat Pattern Questionnaire, which consists of 20 symptom items (10 items to assess cold pattern and 10 to assess heat pattern) [33]. Each item requires only a “yes” or “no” response depending on the patient’s tendencies during the previous week. The total numbers of items that a participant responds ‘yes’ will be the cold or heat pattern score, respectively, for the responder. We will investigate the Cold-Heat Pattern in chronic dry cough patients, as well as the correlation between the cold-heat pattern scores and the efficacy of MMDT.

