##### Yin Deficiency Scale

We will use the validated *yin* deficiency scale developed by Park [34]. This questionnaire consists of 27 items, each of which uses a 7-point Likert scale; the cut-off point was defined as 10 points. We will use the *yin* deficiency scale to evaluate chronic dry cough patients, as well as to investigate the correlation between the *yin* deficiency pattern and the efficacy of MMDT.

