##### MMDT responder/non-responder groups

An MMDT treatment responder is defined as a participant who exhibits a 75 % decrease in cough diary score after 4 weeks of treatment; all other participants in the MMDT treatment group will be included in the non-responder group. We will analyze the correlations between MMDT responder group and all TKM patterns.

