### Statistical analysis

Descriptive statistics will be used for continuous variables, and frequencies for categorical variables. The “last observation carried forward” (LOCF) principle will be used to compensate for missing data. The LOCF principle involves replacement of missing data with the last observed value to obtain a complete database.

When the assumption of normality is satisfied will a *t*-test be used to compare the two groups in terms of the primary outcome (mean cough diary score at week 4). Otherwise, the Mann–Whitney *U*-test will be used. Other continuous variables, such as mean efficacy measurements (cough VAS score or LCQ scores), safety tests (AST, ALT, ALP, TB, GGT, BUN, creatinine, sodium or potassium levels), and biomarkers will be analyzed using the same statistical methods. Associations between the MMDT responders and non-responders with regard to each identified pattern will be estimated using a logistic regression model, which will be adjusted for covariates. All data will be analyzed using SPSS™ for Windows software. The level of significance will be set at a two-sided P value of 0.05.

We, along with a professional statistician, will perform the data analysis for the results.

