## Discussion

Chronic cough is a common symptom in respiratory outpatients, and in an increasing number, the symptom is not eased by conventional treatments. Recent studies have found that substantially fewer patients now respond fully to treatment [7, 37, 38]. Due to the increased patients and limited treatment options, chronic cough is considered a challenging clinical problem.

MMDT is a traditional herbal medicine that has long been used to treat chronic dry cough; however, the evidence regarding the medicine’s efficacy is sparse. We aim to demonstrate the efficacy and safety of MMDT in chronic dry cough via a randomized, placebo-controlled clinical trial that has been designed in accordance with the Consolidated Standards of Reporting Trials guidelines [39]. In addition, we will investigate the relationship between the specifically identified pattern of cough and the effectiveness of MMDT. This trial will provide high-quality evidence on the efficacy and safety of MMDT in the treatment of chronic dry cough. A larger-scale clinical trial to evaluate the effectiveness and safety of MMDT in treating chronic dry cough, based on this study and with specific cough patterns identified, will be possible in future.

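### The stated aim is to relate traditional patterns to MMDT efficacy, but the only analysis given compares responders with non-responders inside the MMDT arm, which cannot separate prognosis from drug effect

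*Protocol article*

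**What the plan says.** The aim is put in terms of drug effect in four places of the protocol article:

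- Pattern Identification for Chronic Cough Questionnaire: "the correlation between chronic cough pattern and the efficacy of MMDT"
- Cold-Heat Pattern Questionnaire: "the correlation between the cold-heat pattern scores and the efficacy of MMDT"
- Yin Deficiency Scale: "the correlation between the *yin* deficiency pattern and the efficacy of MMDT"
- Discussion: "the relationship between the specifically identified pattern of cough and the effectiveness of MMDT"

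The analysis for this aim is in two places. The section on MMDT responder/non-responder groups sets the outcome, "An MMDT treatment responder is defined as a participant who exhibits a 75 % decrease in cough diary score after 4 weeks of treatment", and the comparison group, "all other participants in the MMDT treatment group will be included in the non-responder group". The section Statistical analysis then names the model, a covariate-adjusted logistic regression: "Associations between the MMDT responders and non-responders with regard to each identified pattern will be estimated using a logistic regression model".

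No responder group is defined for placebo, and no treatment-by-pattern term is mentioned. Table 1 nevertheless schedules all three pattern questionnaires at visit 1 and week 4 without restricting them to one arm.

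**The concern.** The Hypothesis section frames efficacy as the contrast between MMDT and placebo. A regression confined to the MMDT arm contains no such contrast. Participants may improve because the cough resolves by itself, because a high score at entry regresses to the mean (entry requires a minimum run-in score), through placebo response, or through the drug. If a pattern is linked to any of the first three, the planned model will show an association that reads as a link with efficacy.

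This is a choice the article states, since the responder section fixes the comparison within one arm. It is not a detail left to an analysis plan that we cannot see. At stake is how the pattern results will be read: a merely prognostic pattern could be reported as marking the patients whom MMDT helps.

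**Working it through.** **Sample size behind the analysis.** The article's own figure reproduces. With effect size 0.85, two-sided alpha 0.05 and power 0.80, an exact two-sample t-test needs 23 per arm (power 0.805). Then 23 / 0.8 = 28.75, rounded up to 29 per arm and 58 in total. The pattern analysis therefore rests on 23 to 29 MMDT participants.

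**What the planned model estimates.** Let D1(x) be the mean improvement under MMDT at pattern score x, and D0(x) the same under placebo. Efficacy at x is D1(x) − D0(x). Since D1(x) = D0(x) + [D1(x) − D0(x)],

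slope of D1 = slope of D0 (prognosis) + slope of D1 − D0 (change in drug effect).

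A within-MMDT regression sees only the left-hand side. Without placebo data the two terms on the right cannot be separated, and adjusting for covariates inside the same arm does not help. This step needs no assumed figures.

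**How often this would mislead.** The assumptions, none of them in the documents, are:

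- 29 per arm;
- pattern score x standard normal;
- improvement y = r·x + √(1 − r²)·e, with e standard normal;
- responders are the 30% with the largest expected improvement;
- no drug effect, and the same r in both arms.

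The planned test is a likelihood-ratio test of x in a logistic model within MMDT. The comparator is the x-by-treatment term in a linear model of y over both arms.

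| r in both arms | Within-MMDT test significant | Two-arm interaction significant |
|---|---|---|
| 0 | about 5% | about 5% |
| 0.3 | about 25% | about 5% |
| 0.4 | about 40% | about 5% |
| 0.5 | about 59% | about 5% |

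**The opposite case.** Now let the pattern matter under MMDT only (r = 0.3, 0.4 or 0.5 against 0 in placebo). The MMDT-arm data have the same distribution as before, so the planned test again gives about 25%, 40% and 59%. It returns the same answer in both situations. The interaction test has about 20%, 34% and 50% power here.

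**A second outcome model.** Assume a 25% responder rate at the mean pattern score, no drug effect, and a prognostic odds ratio of 2 or 3 per SD in both arms. With 29 per arm the within-MMDT test is significant in 36% or 67% of trials; with 23 per arm, in 30% or 57%. A logistic interaction test over both arms stays at about 7% to 8%. The excess over 5% is small-sample error of the likelihood-ratio test; with an odds ratio of 1 the within-arm test also gives 7%.

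**Few events.** Assumed responder rates of 10% to 40% give 23 × 0.1 = 2.3 up to 29 × 0.4 = 11.6 responders. Take 9 responders of 29, a pattern present in half of participants, and no association:

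SE(log OR) = √(2/4.5 + 2/10) = 0.80, and exp(1.96 × 0.80) = 4.8.

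The 95% CI thus extends a factor of 4.8 each way. With 6 responders, √(2/3 + 2/11.5) = 0.92, and the factor is 6.0.

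**The case against.** The best defence is that the trial is labelled exploratory, that the responder and analysis sections speak only of correlations and associations, and that an MMDT-only model can estimate those. This is true of those two sections. It does not cover the questionnaire sections and the Discussion, which name efficacy and effectiveness. The mismatch remains, although rewording the aim would remove it.

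A second objection is that the remedy is weak: at 29 per arm the interaction test would miss a real modifier half the time or more under the assumptions above. That stands and should be stated in the plan. A wide interval for the right quantity is still more useful than a sharper one for the wrong quantity.

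Four stronger readings are tempting, and the article does not support them:

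- **That the 25% to 59% are false-positive rates of the planned test.** They are its power to detect a real association with improvement. With no such association it rejects about 5% of the time. The error lies in calling that association efficacy.
- **That a later trial will select its patterns from this model.** The Discussion says only that a larger trial based on this study, with cough patterns identified, will be possible. It commits to no trial and no selection rule.
- **That all pattern scores enter one overfitted model.** The text refers to each identified pattern, which reads naturally as one model per pattern.
- **That the 75% cut forces a week-4 score of 0 for low baselines.** This needs a single-day whole-number score at week 4. The article fixes a single day only for baseline, and Statistical analysis speaks of a mean score at week 4.

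**Conclusion.** The point holds as a mismatch between aim and analysis. Followed exactly, the plan cannot tell a prognostic pattern from one that changes the effect of MMDT. That conclusion comes from the one-arm design of the analysis and needs no assumed numbers. Its size does need them: about 25% to 59% of trials would show a significant pattern with no drug effect at all, given 30% responders and prognostic correlations of 0.3 to 0.5. A reader with other values in mind should rescale. The 75% split adds imprecision by leaving few events, but the missing comparator is the main fault.

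The plan should be changed, though the matter is moderate. It concerns a secondary aim of an exploratory trial and leaves the primary comparison and the sample size untouched.

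**What to change.** Use both arms. For one pattern at a time, model the continuous week-4 diary score on baseline score, treatment, visit 1 pattern score and the treatment-by-pattern interaction. Report the interaction estimate with its 95% CI and label it hypothesis-generating. Report the 75% responder rate in both arms as descriptive only.

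If the within-MMDT logistic model is kept, describe it wherever it appears as association with improvement among MMDT-treated participants, and drop the words efficacy and effectiveness for that result.

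The visit 1 score is named because the questionnaires are repeated at week 4, after treatment. Which visit was intended is not stated in the article, and this is no criticism of it.

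The cost is a change of wording. No new data are needed, because Table 1 already schedules the pattern questionnaires without arm restriction. The downside to state openly is imprecision: about 20%, 34% and 50% power for a pattern that matters under MMDT only, at correlations of 0.3, 0.4 and 0.5. A non-significant interaction should therefore not be read as absence of one.

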### Sample size calculation

We referred a randomized controlled trial (RCT) that was conducted to demonstrate the clinical efficacy of a herbal medication for the patients with cough variant asthma (CVA) [36]. It was inevitable because no RCTs have been carried out that address the comprehensive chronic cough symptom using a herbal mediation. Furthermore, the main manifestation of CVA is cough lasting more than 8 weeks without any abnormal pulmonary functions; this is very similar to clinical characteristics of the eligible participants recruited in this study.

Using a cough diary score, the CVA study compared the efficacy of a herbal medicine with that of standard therapy (leukotriene receptor antagonist combined with methylxanthine) for 2 weeks. The calculated effect size was 0.699 (α = 0.05, 1-β = 0.8, 2-tailed test). Because of the discrepancy in comparators and study duration between the previous and planned studies, we determined to eliminate the effect of standard therapy and add the effect of longer treatment duration; this resulted in an adjusted effect size of 0.85. Assuming a 20 % dropout rate, and an allocation ratio of 1, we have calculated the necessary sample size to be 58 participants (29 in each group). The above calculations were performed using G*Power™ software (ver. 3.1.9.2) for Mac.

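### Covariate-adjusted logistic models of 75% response in 23 to 29 MMDT patients are likely to overstate real pattern associations, sometimes give no finite estimate, and give p-values that miss the 5% level

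*Protocol article*

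**What the plan says.** Under the heading on MMDT responder and non-responder groups, the Protocol article defines a responder as "a participant who exhibits a 75 % decrease in cough diary score after 4 weeks of treatment" and adds that "all other participants in the MMDT treatment group will be included in the non-responder group". Placebo patients therefore do not enter this analysis. The same section relates responder status to all of the traditional Korean medicine patterns.

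The Statistical analysis section gives the method: for each identified pattern the association "will be estimated using a logistic regression model, which will be adjusted for covariates". It assigns all analyses to SPSS at a two-sided 0.05 level and fills missing values by last observation carried forward. It does not list or count the covariates, name an estimation method for sparse data, or say whether the test is Wald or likelihood-ratio.

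The Sample size calculation section sets 29 patients per group, "Assuming a 20 % dropout rate, and an allocation ratio of 1". No responder rate is given anywhere. The Design section calls the trial exploratory. The Discussion says a larger trial, with specific cough patterns identified, could be based on this one.

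**The concern.** Maximum-likelihood logistic regression needs enough events for each coefficient. Here the events are responders within a single small arm, and the bar is strict. If the baseline (the last run-in day) and the week 4 value are both single-day whole-number totals, a patient starting at 2 must end at or below 0.5, and one starting at 3 at or below 0.75. Either must reach zero. Averaging the week 4 score would ease this slightly.

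With few events and several coefficients, three things can go wrong:

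- estimates of a real association drift away from the null;
- some combination of covariates separates responders from non-responders perfectly, so no finite estimate exists;
- large-sample tests no longer hold their level.

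The pattern-response odds ratios are the natural input when choosing patterns for a later trial. An overstated odds ratio, or a model that fails to converge, would be a poor guide.

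**Working it through.** **Size of the analysis set.** The article's own figure reproduces. A two-sided two-sample t-test at 0.05 with the stated adjusted effect size ("this resulted in an adjusted effect size of 0.85") has power 0.805 at 23 per arm. Then 23 / (1 − 0.20) = 28.75, rounded up to 29 per arm, and 2 × 29 = 58. The responder model therefore has between 23 (completers) and 29 (everyone retained by carrying forward) patients.

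**Responders per coefficient.** The responder rate is an assumption.

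- 29 × 0.20 = 5.8; 29 × 0.30 = 8.7; 29 × 0.40 = 11.6.
- 23 × 0.20 = 4.6; 23 × 0.40 = 9.2.
- One pattern plus 1 to 4 covariates is 2 to 5 coefficients besides the intercept. At 29 patients that is 5.8 / 2 = 2.9 down to 5.8 / 5 = 1.2 responders per coefficient at 20% response, and 11.6 / 2 = 5.8 down to 11.6 / 5 = 2.3 at 40%.

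**Simulation.** Assumed: a standard normal pattern score, covariates unrelated to response, response 20-40%, 1 to 4 covariates, 23 or 29 patients. The true odds ratio is either 1 or 2 per standard deviation (log odds ratio ln 2 = 0.693). Ordinary maximum likelihood is fitted, and means and medians are over finite fits.

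*Overstatement = estimate / 0.693 − 1.* Over the whole grid:

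- Mean log odds ratio 0.85 to 1.22: 0.85 / 0.693 − 1 = 23%; 1.22 / 0.693 − 1 = 76%.
- Median 0.76 to 0.94: 0.76 / 0.693 − 1 = 10%; 0.94 / 0.693 − 1 = 36%.

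A separate set of runs at 29 patients shows how the mean moves. Its figures can differ from the grid by a few hundredths through simulation error.

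| Response | 1 covariate | 2 covariates | 4 covariates |
|---|---|---|---|
| 20% | 0.88 | 0.97 | 1.14 |
| 30% | 0.89 | 0.96 | 1.16 |
| 40% | 0.84 | 0.94 | 1.04 |

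The number of covariates drives the overstatement more than the responder rate does, and it persists at 40% response.

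*No finite estimate.* 0-14% of fits at 29 patients and 0-27% at 23, worst at 20% response with several covariates. At 20% response and one covariate it is about 1% at 29 patients. A wider check that also allowed a binary pattern gave 1-2% at 40% response and 42-57% at 10% response, both with two covariates and 29 patients.

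*Rejection when there is no association, nominal 5%.* Likelihood-ratio about 6-10%; Wald about 0.3-4%. The wider check, including 10% response, gave 7-19% and 0-5% in adjusted models.

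*Average estimate when there is no association.* Odds ratio 0.98 to 1.03 for a continuous pattern, so no bias.

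**Firth's penalised likelihood, one covariate, same grid.** Mean log odds ratio 0.66 to 0.73 against 0.693, rejection under no association 3-5%, power 16-35% against 4-31% for the Wald test.

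**The case against.** A reader might infer that the plan produces too many false positives. The article does not support that. It names no test, and the excess appears only with likelihood-ratio tests. With Wald tests the rate is at or below 5%, and the cost is lost power. Nominal 95% Wald intervals covered the truth 96-98% of the time in runs with up to two covariates. Nor can one say that the odds ratios are inflated in general: with no true association there is no average bias.

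The low responder count and the use of ordinary maximum likelihood are also inferences. The article states no rate, covariate count or estimation method, does not rule out exact or penalised fitting, and involves a professional statistician. Such details are often left to an analysis plan that is not shown here. The mean is the harsher summary, because a few nearly separated fits pull it up; the medians are milder. Patterns do not appear in the stated objective or hypothesis, and the Discussion sets no rule for going on to a larger trial.

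Most of this stands and limits the point. It does not remove it. The article does fix a logistic model with covariates, in the plural, for each pattern, in one arm of at most 29. An analysis plan that only listed the covariates would still carry out that model on those patients. The overstatement remains across the whole assumed range of response, and neither customary test holds its level.

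**Conclusion.** The concern holds in a limited form. If the stated model is fitted by ordinary maximum likelihood, a real pattern association of log odds ratio 0.69 is overstated by about 23-76% on the mean and 10-36% on the median. Up to 14% of fits at 29 patients, and up to 27% at 23, have no finite estimate. P-values are liberal or conservative according to a test that the article does not name.

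These sizes rest on assumed response of 20-40%, 1 to 4 covariates unrelated to response, and a continuous pattern score. Non-finite fits become rare with one covariate or at 40% response, and common if response is near 10%.

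This is a minor point about a secondary analysis in an exploratory trial. The primary comparison and the sample size of 58 are not affected.

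**What to change.** In the Statistical analysis section, replace the covariate-adjusted logistic model with one model per baseline pattern score, fitted by Firth's penalised likelihood. Take confidence intervals and tests from the profile penalised likelihood. Allow at most one pre-specified covariate, the baseline cough diary score. Report the number of responders beside each estimate. Exact logistic regression, or an analysis of the continuous change in diary score, would also avoid the problem; Firth's method keeps the planned responder question and always returned a finite estimate in the checks.

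Costs: no adjustment for further covariates, and software beyond the planned SPSS analysis may be needed. Nominal power is lower than with the liberal likelihood-ratio test (for one setting, about 24% against 31-35%), but higher than with the Wald test. Power stays low whichever method is used, so the results should be read as hypothesis-generating. Recruitment, visits and sample size do not change.

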## Discussion

Chronic cough is a common symptom in respiratory outpatients, and in an increasing number, the symptom is not eased by conventional treatments. Recent studies have found that substantially fewer patients now respond fully to treatment [7, 37, 38]. Due to the increased patients and limited treatment options, chronic cough is considered a challenging clinical problem.

MMDT is a traditional herbal medicine that has long been used to treat chronic dry cough; however, the evidence regarding the medicine’s efficacy is sparse. We aim to demonstrate the efficacy and safety of MMDT in chronic dry cough via a randomized, placebo-controlled clinical trial that has been designed in accordance with the Consolidated Standards of Reporting Trials guidelines [39]. In addition, we will investigate the relationship between the specifically identified pattern of cough and the effectiveness of MMDT. This trial will provide high-quality evidence on the efficacy and safety of MMDT in the treatment of chronic dry cough. A larger-scale clinical trial to evaluate the effectiveness and safety of MMDT in treating chronic dry cough, based on this study and with specific cough patterns identified, will be possible in future.

